## Methods/design

### Study design

This study will be implemented as a two-arm, cluster-randomised controlled trial (RCT), with an intervention condition (Sources of Strength program) and 24-month wait-list control condition. Measurements will be taken on four occasions: pre-intervention, post-intervention (after 3 months of messaging), and in two follow-ups at the end of each school year (approximately 6- and 18-month follow-up). This study was granted ethical approval by the Australian National University Human Research Ethics Committee (protocol number 2015/199) and the individual State and Territory education departments (Catholic Education Office Archdiocese of Canberra & Goulburn, ACT Government Education and Training Directorate, and the NSW Government Department of Education) responsible for schools in the recruitment districts.

### Recruitment

It is planned to recruit 16 schools from the Australian Capital Territory (ACT) and New South Wales (NSW), Australia, through letters of invitation and direct contact from the research team. All students aged 12–15 years in participating schools will be invited to participate in the research, while a select group of students representing each year level (7–9) from the intervention schools will also be invited to undertake the Sources of Strength peer-leadership program. Students will be invited to peer-leadership positions based on referrals from school staff identifying their influence among their peer groups. Information and consent forms will be distributed to all students and their parent/guardian prior to the trial commencing, with written or verbal informed consent required from both. All students in the intervention schools will potentially be exposed to the school-based messaging undertaken by the peer leaders. However, only consenting students will complete the trial questionnaires. All peer leaders will require consent to participate in the Sources of Strength peer leadership training and to complete the trial questionnaires. Adult advisors in the intervention schools will also receive training to assist and support the peer leaders in their role and will receive ongoing support through webinars hosted by the US Sources of Strength team.

### Randomisation

Each participating school (cluster) will be randomised to the intervention or wait-list control condition. Cluster randomisation will be undertaken for administrative convenience, to avoid contamination of the wait-list control condition and for the ecological validity of providing the intervention at the school level. School randomisation will be carried out by a statistician not involved in the day-to-day conduct of the trial according to ICH Guidelines [18]. As whole schools will be allocated to a single condition (cluster design), a minimisation approach [19, 20] will be used to ensure balance across conditions on the basis of school location (ACT/NSW), school type (private/public), number of students, and sex ratio.

### Procedure

Prior to the commencement of the project in each school, trial liaison managers located in the ACT and NSW will meet with each school to introduce the project to the wider school staff population and to prepare specific clinical protocols within each school. These protocols will detail the processes that will be undertaken if a student reports high levels of suicidality in the trial questionnaires. Student questionnaires will be viewed by the trial liaison managers following their completion to identify ‘at-risk’ respondents. School psychologists, counsellors, or a nominated staff member will be notified of ‘at-risk’ students, and they will follow up with them in accordance with usual school procedures. Students will also be provided with help-seeking contacts (e.g. school psychologist/counsellor or general practitioner) and information (e.g. telephone helplines or websites).

Following the development of clinical protocols, schools allocated to the intervention condition will nominate school staff to act as adult advisors for the Sources of Strength program. The selected staff will be provided with training in the Sources of Strength program, and will undertake the nomination process for peer leaders. At the commencement of the study, all consenting students in participating schools (both intervention and control) will be invited to complete a pre-intervention questionnaire. Questionnaire completion will be co-ordinated by the trial liaison managers to ensure standardisation and student privacy. Questionnaires will be delivered during school time and will be completed online or via paper and pencil, depending on school preference and resourcing. The assessments will take approximately 30 to 40 minutes to complete and have been designed to reduce participant burden. All data will be securely stored at The Australian National University, with access to the data restricted to trial personnel and investigators.

Following completion of the pre-intervention questionnaire, students in intervention condition schools who have been nominated as peer leaders will undertake the Sources of Strength peer-leadership training (4–6 hours over 1 day). Following this training, the peer leaders will meet with the adult advisors in their school on a fortnightly basis to plan and undertake 3 months of whole-school messaging. Students in the wait-list control condition schools will undertake usual school activities during this period.

At the completion of the messaging phase, the post-intervention questionnaire will be administered to all students. A short survey will also be administered to all staff in intervention condition schools to assess the reach of the whole-school messaging and youth-adult connections. A 6-month follow-up questionnaire will also be administered to all students towards the end of the first year of the program.

In the second year of the project, a refresher Sources of Strength peer leadership training will be provided, with new adult advisors and peer leaders invited to participate alongside previous participants. This will be followed by a second 3-month whole-school messaging phase. A final 18-month follow-up questionnaire will be conducted at the end of the second year. After the completion of all questionnaires, schools in the wait-list control condition will be offered the Sources of Strength program, including the training of adult advisors and peer leaders, but questionnaires will not be administered. Figure 1 presents the flow of participants in the trial (See Additional file 1: Attachment A for SPIRIT Checklist).

**Fig. 1 Fig1:**
[figure not shown]
Flow of participants

### Intervention

The Sources of Strength program will consist of four phases in the first year of implementation. The first phase will be school and community preparation and will involve a 1-hour presentation to all school staff, the nomination and training (4–6 hours) of 2–3 staff members per school to act as adult advisors, and the development of a clinical protocol that outlines the school’s response to suicidal behaviours. The role of adult advisors will be to support and guide the peer leaders to conduct safe suicide prevention messaging.

The second phase of the program will be the nomination and training of peer leaders. Schools will be invited to nominate 2–10 % (maximum of 50 students) of their students as peer leaders, selecting key opinion leaders in diverse groups. The focus of peer leader training (4–5 hours) will be on interactive learning about the eight protective ‘sources of strength’, skills for increasing these resources for themselves and others in times of need, and engaging ‘trusted adults’ to help distressed and suicidal peers. The training program will focus on positivity, influence, and leadership, rather than purely on suicide prevention.

The third phase of the intervention will be whole-school messaging, which will entail activities to increase connectedness and will be undertaken over a 3-month period. In the first year, the messaging will involve (1) engaging ‘trusted adults’ by contacting them and acknowledging them as such; (2) encouraging friends to identify their ‘trusted adults’ and sharing these on a ‘wall of trust’; (3) undertaking pre-rehearsed classroom presentations to spread the sources of strength message by modelling how they have overcome adversity using positive coping and how they would engage a trusted adult for support for a suicidal friend; and (4) wider school ‘hope, help, and strength’ messaging using posters, public service announcements, videos and messages posted on social media sites (creating their own materials or using those available on the Sources of Strength Facebook page) to further disseminate the messages of the Sources of Strength program. Messaging will be empowering and strength-based, avoiding trauma, shock, or negative messaging, which could instil hopelessness. Peer leaders will meet fortnightly with the adult advisors to plan and approve messaging activities.

The final phase will be a celebration to recognise the peer leaders for their roles and accomplishments. In the second year, the program will be continued with the addition of new adult advisors and peer leaders alongside previous participants, and a repeat of the whole-school messaging. The reach and sophistication of messaging is expected to increase in the second year, as peer leaders become more comfortable and confident in their role. The wait-list control condition will continue usual school activities during the intervention phase of the trial and will receive the program after the follow-up periods.

### Assessments

Table 1 presents the scales that will be administered at each measurement occasion in the Australian Sources of Strength trial. It is noted that the measures included are relevant to different, sometimes multiple, study aims. All measures have previously been evaluated with adolescent samples and have good psychometric properties.

**Table 1 Tab1:** Questionnaire scales for the Sources of Strength trial

	Pre-intervention	Post-intervention	6-month follow-up	18-month follow-up	No. of items
Demographics	✓	✓	✓	✓	6
Help-seeking Measures					
Adapted GHSQ	✓	✓	✓	✓	11
Adapted AHSQ	✓	✓	✓	✓	12
Help-seeking from adults	✓	✓	✓	✓	4
Help-seeking from adults at school	✓	✓	✓	✓	4
Reject codes of silence	✓	✓	✓	✓	4
Adult help for suicidal youth	✓	✓	✓	✓	4
Trusted adults at school	✓	✓	✓	✓	4
Referral of distressed peers	✓	✓	✓	✓	5
Positive coping					
SWEMWBS	✓	✓	✓	✓	7
SoS coping	✓	✓	✓	✓	8
Social support	✓	✓	✓	✓	15
Mastery	✓	✓	✓	✓	7
Suicidality					
YRBS	✓		✓	✓	4
SIDAS	✓	✓	✓	✓	5
Suicide risk models					
INQ	✓	✓	✓	✓	15
ACSS	✓	✓	✓	✓	7
Entrapment	✓	✓	✓	✓	4
Risk and protective factors					
Self-harm	✓	✓	✓	✓	3
SOSS	✓	✓	✓	✓	16
LOSS	✓				12
DQ5	✓	✓	✓	✓	5
MDI	✓	✓	✓	✓	13
SCARED-GAD	✓	✓	✓	✓	9
Bullying	✓	✓	✓	✓	3
Peer integration at school	✓	✓	✓	✓	4
School identification	✓				2
SURPS-23	✓				23
RTSHIA (RT)	✓	✓	✓	✓	8
Social network variables					
No. of friends	✓	✓	✓	✓	3
No. of trusted adults	✓	✓	✓	✓	2
Naming trusted adults	✓	✓	✓	✓	9
Naming close friends	✓	✓	✓	✓	21
Intervention engagement					
Intervention reach^a^		✓		✓	11
Fidelity questions^b^		✓		✓	6

*ACCS* Acquired Capability for Suicide Scale, *AHSQ* Actual Help-Seeking Questionnaire, *DQ5* Distress Questionnaire-5, *GHSQ* General Help-Seeking Questionnaire, *INQ* Interpersonal Needs Questionnaire, *LOSS* Literacy of Suicide Scale, *MDI* Major Depression Inventory, *RTSHIA* (*RT*) Risk Taking and Self-Harm Inventory for Adolescents – Risk-Taking Scale, *SCARED*-*GAD* Screen for Child Anxiety Related Emotional Disorders, *SIDAS* Suicidal Ideation Attributes Scale, *SOSS* Stigma of Suicide Scale, *SoS* Sources of Strength, *SURPS*-*23* Substance Use Risk Profile Scale, *SWEMWBS* The Short Warwick-Edinburgh Mental Well-being Scale, *YRBS* Youth Risk Behaviour Survey

^a^Only students in intervention schools respond to these questions

^b^Only peer leaders in intervention schools respond to these questions

### Demographic variables

The following demographic variables will be measured: age, sex, grade, language spoken at home, and school name.

### Help-seeking

The primary aim of the Sources of Strength program is to promote help-seeking from a trusted adult in times of distress. A series of measures are therefore included in the questionnaires that assess help-seeking intentions, help-seeking behaviour, and the perceived usefulness of adult help, attitudes towards adult help, the referral of distressed peers, and the availability of adult help (for suicidal youth and more generally). The adapted version of the *General Help*-*Seeking Questionnaire* (GHSQ) [21, 22] is the primary outcome measure in the current study. It assesses intentions to seek help for personal or emotional problems from 11 different formal and informal sources (e.g. friend, parent, psychologist, or teacher). Respondents indicate how likely they are to seek help from each of the sources on a scale ranging from 1 (extremely unlikely) to 7 (extremely likely).

The adapted *Actual Help*-*Seeking Questionnaire* (AHSQ) [22, 23], and subsequent help-seeking measures, are secondary outcome measures that further explore the impact of the program on help-seeking. The AHSQ assesses recent actual help-seeking behaviour and consists of the same 11 sources of help as the GHSQ, in which the respondent either does or does not report having sought help from for a mental health problem in the past 3 months. In addition to the AHSQ, *actual help*-*seeking from adults* is measured by four items (yes/no) that assess the experience of help-seeking from adults, conditional on responses to the AHSQ. If students indicate that they have sought help from at least one adult for a mental-health problem on the AHSQ, then four questions will be presented asking whether any of the adults that they have had contact with have made them feel supported, helped them get through the situation, made the situation worse, or made them more likely to seek further help from adults. These items were drawn from the previous US Sources of Strength trial [10].

Help-seeking attitudes are assessed by two measures including the *help*-*seeking from adults at school* [24], which is a four-item measure derived from the previous US Sources of Strength trial. The measure assesses attitudes and perceived norms about seeking help from adults at school on a scale from 1 (strongly disagree) to 4 (strongly agree). The items on this scale enquire as to whether, if really upset and needing help, a student would talk to a counsellor or other adult at school, whether they believe these adults could help, and whether friends and family would want them to seek help. Items on this scale are summed, with higher scores reflecting more positive help-seeking from adults at school. A second four-item scale (r*eject codes of silence*) will measure student attitudes toward overcoming secrecy barriers to engaging adult help for suicidal peers. Items are responded to on a four-point scale ranging from 1 (strongly disagree) to 4 (strongly agree), with higher scores indicative of more positive intentions to get help for suicidal friends and resist requests for secrecy [8, 10].

A further two scales, also from the previous US Sources of Strength trial [10], assess the availability of adult help. The first four-item scale specifically assesses the availability of *adult help for suicidal youth*, enquiring about whether youth know adults who could help a friend thinking of suicide, whether their school has people who can help students going through hard times, whether they can think of an adult they trust enough to help a suicidal friend, and whether students with problems can get help from adults in their school. Items on this scale are responded to on a four-point scale ranging from 1 (strongly disagree) to 4 (strongly agree). Higher scores are indicative of a perception of strong adult support being available for suicidal youth in the school. The second four-item scale assesses *trusted adults at school* [25]: i.e. adolescents’ perception of having an adult to turn to for open, honest, and safe communication. Items within this scale (e.g. ‘At my school there is an adult who listens to what I have to say’) are also rated on a four-point scale ranging from 1 (strongly disagree) to 4 (strongly agree), with higher scores suggestive of students having adults at school that they feel they can trust and talk to about problems.

Finally, five items will be administered to assess the respondent’s friends’ suicide risk and the *referral of distressed peers*. These questions assess help-seeking behaviour by friends considering suicide (e.g. ‘Have any of your friends told you they were thinking of killing themselves’) and referral of friends to help sources (e.g. ‘I told a friend to get help because of emotional or behaviour problems’). These items are adapted from the *Referred Distressed Peers to Adults Scale* [10] and from questions being used in the current US evaluation of the Sources of Strength program.

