#### Secondary aims

The secondary aims are as follows:To test the effectiveness of the Sources of Strength intervention for increasing help-seeking intentions for suicide at 6-month follow-upTo test the effectiveness of the Sources of Strength program for (a) increasing actual help-seeking behaviour and the usefulness of adult help, (b) improving attitudes and norms towards adult help, (c) greater referral of suicidal peers, and (d) increased availability of adult help, at post-intervention and 6-month follow-upTo test the effectiveness of the Sources of Strength program for increasing positive coping (mental wellbeing, Sources of Strength (SoS) coping, social support, and mastery) at post-intervention and 6-month follow-upTo test the effectiveness of the Sources of Strength program for reducing suicidal thoughts and behaviours (plans and attempts) at post-intervention and 6-month follow-upTo test the impact of the Sources of Strength program on thwarted belongingness at post-intervention and 6-month follow-upTo test if the Sources of Strength intervention effects are increased at 18 months following the second year of program implementation

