#### Trial hypotheses

At post-intervention and 6-month follow-up, participants in those schools receiving the Sources of Strength program, relative to participants in the wait-list control schools, will have:Increased help-seeking intentions for suicide(a) Increased actual help-seeking behaviour for suicide, more positive attitudes and norms associated with adult help for suicide, increased referral of suicidal peers, and greater perceived availability of adult help for suicidal peers(b) Increased positive coping, which is demonstrated by higher mental wellbeing, greater endorsement of SoS coping, more positive social support and higher mastery(c) Lower levels of suicidal ideation, plans, and attempts(d) Decreased levels of thwarted belongingness, thus reducing suicide susceptibility

Furthermore:2.(e) Within-school effects at intervention schools will be stronger at 18 months (as the messaging program matures) than at 6 months.

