### Statistical analysis

Analyses of continuous measures will be undertaken on an intent-to-treat basis, including all participants randomised regardless of treatment actually received or withdrawal from the study. Mixed-model repeated-measures analyses will be used because of the ability of this approach to include participants with missing data without using biased techniques, such as last observation carried forward [47]. In addition, by incorporating appropriate random effects for schools, this approach can accommodate and assess the magnitude and significance of clustering effects. The primary aim will be evaluated by a contrast examining change in help seeking intentions from pre-intervention to post-intervention in the Sources of Strength condition compared to that in the wait-list control condition. For suicide attempts and other dichotomous outcomes, a comparable binary mixed modelling approach [48] will be used. Differences in relative risk for incidence of suicide attempt from baseline to the 6- and 18-month follow-ups will be assessed. Mediators of intervention outcome including suicidal ideation, depressive symptoms and exposure to school-based messaging will be explored using interaction terms in mixed effects models and using latent class analyses [49]. Models of suicide risk will be developed using regression analyses and structural equation models, testing the Interpersonal Theory of Suicidal Behavior framework and examining the role of additional psychosocial and demographic risk factors. Social network factors will be assessed in a subset of two schools (one control and one intervention), evaluating up to seven connections per student at pre- and post-intervention, to estimate a range of network indices of density, reciprocity, clustering and individual centrality. Change in social network characteristics as a function of intervention condition will be tested. During the messaging phase, engagement with social media messages posted by peer leaders at the intervention schools will be analysed by categorising posts and assessing the types of messaging that best engage students by measuring reach through likes, shares, and comments. This sub-study measures ‘digital footprint’ behaviour, and thus complements the self-report measures of connectivity.

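### The usefulness-of-adult-help items go only to students who sought adult help, so a between-arm test of them is open to selection bias in either direction

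*Protocol article*

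**What the plan says.** Under Secondary aims, the program is to be tested at post-intervention and 6-month follow-up for "increasing actual help-seeking behaviour and the usefulness of adult help". Under Help-seeking, the AHSQ and "subsequent help-seeking measures, are secondary outcome measures that further explore the impact of the program on help-seeking". Usefulness is covered by four yes/no items "that assess the experience of help-seeking from adults, conditional on responses to the AHSQ". The gate is explicit: "If students indicate that they have sought help from at least one adult for a mental-health problem on the AHSQ, then four questions" are shown. They ask whether any of the adults made the student feel supported, helped with the situation, made it worse, or left the student more inclined to go back to adults. The AHSQ records, for each source, whether the student reports "having sought help from for a mental health problem in the past 3 months".

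The same subsection opens by saying: "The primary aim of the Sources of Strength program is to promote help-seeking from a trusted adult in times of distress". The first item in Trial hypothesis 2(a) is: "Increased actual help-seeking behaviour for suicide".

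For the analysis, the Statistical analysis section says: "For suicide attempts and other dichotomous outcomes, a comparable binary mixed modelling approach" will be used. It makes no separate provision for a dichotomous outcome that is recorded only in some students.

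**The concern.** The two halves of the secondary aim pull against each other. If the program brings more students to adults, the students who answer the usefulness items in intervention schools are no longer the counterparts of those who answer in control schools. The extra respondents may be more hesitant or more distressed, or they may have gone to better-chosen adults. Either way, the proportion answering yes among seekers can differ between arms although no student's experience of adult help has changed.

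School random effects do not repair this, because the imbalance is between kinds of student within schools. Baseline values help little, because a student who had not sought adult help before the intervention has no baseline usefulness answer. The article's missing-data argument for mixed models does not help either: a non-seeker's rating is undefined, not missing.

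At stake is a reported finding that adults became more or less helpful under a suicide-prevention program, when all that changed was who was asked.

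**Working it through.** **No plan figure to reproduce.** The article gives no rate of adult help-seeking and no rate of yes answers. Every rate below is an assumption, chosen to show direction and rough scale.

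**Set-up.** Let pC and pT be the proportions seeking adult help in control and intervention schools. Assume the program adds seekers and removes none. Let q be the proportion of yes answers among students who would seek help anyway, the same in both arms, so the true effect on usefulness is zero. Let qi be the proportion among the added seekers.

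- Yes among seekers, control: q.
- Yes among seekers, intervention: [pC × q + (pT - pC) × qi] / pT.
- Spurious difference: (pT - pC) × (qi - q) / pT.

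The last line is zero only if pT = pC or qi = q.

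**Worked case.** pC = 0.20, pT = 0.25, q = 0.80, qi = 0.60:

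- Among seekers, intervention: (0.20 × 0.80 + 0.05 × 0.60) / 0.25 = 0.19 / 0.25 = 76.0%, against 80.0% in control. The difference is -4.0 points.
- Over all students, sought help and answered yes: 0.20 × 0.80 = 16.0% in control, 19.0% in intervention.

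The seekers-only comparison shows a loss, while more students in total had a useful contact with an adult.

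**Range, with q = 0.80.** Difference among seekers in points; in brackets, the all-student proportion in intervention schools (control 16.0% throughout):

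| Seeking, control vs intervention | qi = 0.60 | qi = 0.80 | qi = 0.90 |
|---|---|---|---|
| 20% vs 22% | -1.8 (17.2%) | 0 (17.6%) | +0.9 (17.8%) |
| 20% vs 25% | -4.0 (19.0%) | 0 (20.0%) | +2.0 (20.5%) |
| 20% vs 30% | -6.7 (22.0%) | 0 (24.0%) | +3.3 (25.0%) |

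**Effect on a nominal 5% test.** Take 2,400 per arm in eight schools, less 20% attrition: 1,920 per arm. Assume the plan's ICC of 0.04 also applies to these items. For 20% vs 25% with qi = 0.60:

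- Seekers: 384 and 480, or 48 and 60 per school.
- Design effects: 1 + 47 × 0.04 = 2.88 and 1 + 59 × 0.04 = 3.36.
- Standard error: √(0.16 × 2.88/384 + 0.1824 × 3.36/480) = √(0.00120 + 0.00128) = 0.050.
- A shift of -0.040 then rejects with probability of about 0.13 by the normal approximation.

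The same steps give about 0.27 for 20% vs 30% with qi = 0.60, and 0.05 to 0.07 in the 20% vs 22% row.

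**The made-worse item.** Suppose 10% of seekers in both arms say an adult made things worse. Over all students this is 0.20 × 0.10 = 2.0% against 0.25 × 0.10 = 2.5%. The rate rises through seeking alone.

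**The case against.** The strongest reply is that the article states a skip pattern and not an analysis. It gives no denominator for these items, and the Statistical analysis section does not name them. An unseen SAP could score non-seekers as 0 or label the comparison descriptive. That is possible, but the article does fix the gated measurement, the effectiveness aim and a between-arm model for dichotomous outcomes, and states the alternative scoring nowhere. Followed as written, the text leads to a test among seekers.

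Other parts of the reply stand. Usefulness appears in the aims but is not named in the Trial hypotheses. A related scale on help from adults at school, which includes whether those adults could help, is not described as gated. All-student scoring has its own limits: the positive items also rise with seeking alone (16.0% to 20.0% in the 20% vs 25% row when qi = q), and the made-worse item does so in a way that looks like harm.

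Two stronger readings are tempting. A reader might infer that the comparison is certainly biased; the document gives no rates from which to show that. A reader might also infer that the article's intent-to-treat commitment is broken. That sentence is confined to continuous measures, and these items are yes/no, so it makes no claim about them.

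**Conclusion.** The point holds in a limited form. A between-arm test of the usefulness items among help-seekers is not protected by randomisation and is open to selection bias in either direction. With q = 0.80 and seeking raised from 20% to between 22% and 30%, the spurious difference lies between -6.7 and +3.3 points. These figures rest wholly on assumed rates and on the program adding seekers without removing any. The bias disappears if the program does not change who seeks adult help, or if added seekers rate adults as other seekers do.

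It touches one part of one secondary aim. The GHSQ, as primary outcome, and the AHSQ are not gated in this way. This is an inexpensive improvement to a secondary analysis, not a threat to the trial's main conclusion.

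**What to change.** - For the three positive items (felt supported, helped through it, more inclined to seek adult help again), score every student 1 if they sought adult help in the past 3 months and answered yes, and 0 otherwise. Compare arms with the planned binary mixed model.
- Interpret each result as a joint seeking-and-useful outcome, and present it beside the AHSQ seeking rate, because it can rise through seeking alone.
- Report all four items among help-seekers by arm as description, without a between-arm effectiveness test.
- Do not read an all-student rate of the made-worse item as harm from the program.

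The cost is a short scoring and analysis statement, with no change to the questionnaire or to data collection. What is given up is a tested claim about usefulness separate from seeking, and the gated items do not support a randomised test of that.
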